**Fig. 1 Fig1:**
[figure not shown]
CONSORT flow diagram of participant timeline [14]

## Methods: assignment of interventions

### Randomisation and allocation

Following telephone screening and verbal consent, eligible participants will be allocated to groups using a simple randomisation procedure via an online web-based system. Allocation will be communicated to participants by email. Due to the nature of the intervention, neither participants nor facilitators can be blinded to group assignment; however, participants will be asked not to disclose their allocation during outcome assessments. Following allocation, participants will receive an electronic information sheet and consent form, with all further correspondence conducted via email unless otherwise requested. We acknowledge how simple randomisation may result in unequal group sizes or imbalances in baseline characteristics, particularly in smaller samples; these will be examined descriptively and considered when interpreting exploratory outcomes [39].

## Methods: data collection, management, and analysis

All data will be stored on The Loss Foundation’s secure server. Survey administration will be automated through Qualtrics. Data will be pseudonymised and managed in accordance with the GDPR. Only the research team, including the principal investigator ([name]) and supervisor ([name] [name]), will have access to anonymised data.

### Statistical analysis

All analyses will be conducted using JASP (2025, version 0.19.3) [18]. Data will be screened for outliers, missingness, and normality. Where assumptions for parametric models are moderately violated, we will proceed with them (as they are robust to mild non-normality), supplemented by non-parametric sensitivity analyses.

#### Primary analysis (feasibility outcomes)

The primary focus of this pilot trial is the evaluation of feasibility and acceptability outcomes, including recruitment and consent rates, retention and attrition, session attendance and adherence, and completeness of outcome data. These outcomes will be summarised descriptively using counts, percentages, and, where appropriate, confidence intervals. These data will be used to inform progression criteria and future trial design.

Progression criteria for a future definitive trial will be pre-specified using a traffic-light framework with green (go), amber (amend), and red (stop) thresholds. Thresholds were guided by best practice recommendations for external pilot trials [4] and informed by the expertise of the principal investigator and supervisor.

#### Exploratory secondary analysis (between-group)

Clinical outcomes (e.g. grief intensity, post-traumatic stress, depression, anxiety, self-compassion and social disconnection) will be analysed between the Non-WL and WL control groups only. The primary estimand is the difference in change between groups from baseline during the first three months. Linear mixed-effects models (or mixed ANOVA) will be used with fixed effects for group, time (baseline, three month follow up), and their interaction (group × time), and a random intercept for participants. The group × time interaction will index the treatment effect. Baseline scores may be included as covariates in an ANCOVA framework where appropriate. Effect sizes (standardised mean differences) and 95% confidence intervals will be reported.

If a sample size approaches *n* = 100, exploratory predictor analyses may examine associations between baseline characteristics (e.g. demographics, baseline severity) and outcome changes. This would be to inform outcome selection, covariate choice, and sample size calculations for a future trial. These analyses are descriptive and will not be used to draw confirmatory conclusions [24, 52].

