## Methods: participants, interventions, and outcomes

### Trial design and setting

This study will use a longitudinal pilot RCT design to evaluate the feasibility, acceptability, and preliminary effectiveness of an online therapeutic bereavement group for adults bereaved by cancer. Participants will be randomly allocated to one of two parallel conditions: non-waitlist (Non-WL) whereby participants will access the intervention immediately and waitlist control (WL) whereby participants will receive the same intervention after a three-month delay.

Four groups will run online (two Non-WL and two WL) to ensure clinically appropriate group sizes and maximise therapeutic benefits. The groups will be identical in content and delivered in two parallel series to accommodate the WL design, enabling sufficient data collection within the study timeframe. The Non-WL groups will run first, over a period of 12 weeks comprising a total of eight online sessions. The first four sessions will take place weekly and the remaining four sessions fortnightly, allowing participants time to consolidate learning and apply skills between sessions. The WL groups will begin 3 months later, following the same schedule. Please see Supplementary Material 2: Appendix D for the research protocol.

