#### Facilitation and fidelity

Each group will include approximately 20 to 25 participants. Sessions will be co-facilitated by two trained clinicians (clinical psychologists and cognitive behavioural therapists) who volunteer at The Loss Foundation and have prior experience in bereavement support and group facilitation. All facilitators will complete a half-day standardised training and receive ongoing clinical supervision from [name] [name].

To ensure intervention fidelity, facilitators will adhere to a manualised protocol specifying content, structure, and timing. Fidelity checklists will be completed after each session, and any deviations or adaptations will be documented. Attendance will be tracked using Zoom reports, and participants will complete brief reflective exercises to reinforce learning and monitor engagement. The only expected modifications to the intervention relate to enhancing accessibility, for example for participants who are visually impaired.

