### Sample size

A total of 100 adults bereaved by cancer (50 per arm) will be recruited. As a pilot RCT, the sample size was selected to estimate key feasibility parameters (recruitment, consent, randomisation, adherence, retention, acceptability, and data completeness) with acceptable precision, in line with current guidance on pilot trial sample size determination, rather than to evaluate clinical effectiveness [14, 51, 54]. Although not powered for formal efficacy testing, the sample permits exploration of medium-to-large between-group differences, with any observed outcomes interpreted cautiously to inform outcome selection, variance estimates, and sample size planning for a future definitive RCT.

While online therapeutic groups are often smaller, anticipated attrition and high demand support initial recruitment of 25 participants per group. This size allows structured facilitation, participant engagement, and safety, consistent with prior evidence that slightly larger groups remain effective when appropriately organised [43]. Sessions integrate guided sharing, individual reflection, feedback monitoring, and psychoeducational content, making this format feasible while generating meaningful feasibility data to guide a future definitive RCT.

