### Recruitment

The Loss Foundation will send a promotional advert via their mailing list, website, and social media (Facebook and Instagram), inviting individuals to take part in the bereavement therapy groups. Please see Supplementary Material 2: Appendix A for a copy of the advertisement material. Basic information about the study and how to register interest will be displayed on their website and social media accounts. In addition, an email with a link to register interest in the study will be sent to all individuals on their mailing list. An email address for a member of the research team will be provided in these adverts. Participants will self-identify themselves by registering via a secure link and providing their preferred contact details. After self-referral, they will be invited to take part in a screening telephone call with a member of the research team to allow the team to fully explain the trial, to confirm eligibility, and to answer any questions. Following the screening phone call, individuals who give verbal consent for participation and who fulfil the inclusion criteria will be randomised in a 1:1 ratio to either the Non-WL or WL control groups. After randomisation and confirmation of their space in the programme, they will be invited to read the information sheet and sign the electronic consent form to give informed consent prior to participating (please see Supplementary Material 2: Appendix B). The information sheet given to participants includes details on randomisation to start the group immediately (Non-WL) or three months later (WL). Part of the eligibility criteria consists of participants giving informed consent to willingly be randomised including experiencing a delay in the intervention. Participants that do not consent to this will be excluded from the sample. Apart from the initial telephone screening, all correspondence with participants by the research team will be via email, unless the participant requests a telephone call or remote meeting to ask questions.

Participants will be recruited and assessed at baseline from February 2025 with data collection expected to finish in November 2025. Figure 1 shows the CONSORT flow diagram of the study participants.

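### The between-arm model ignores that only the immediate-start arm is treated in two shared therapy groups, so its 95% confidence intervals are too narrow if outcomes cluster by group

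*Protocol article*

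**What the plan says.** The protocol article randomises individuals: they "will be randomised in a 1:1 ratio to either the Non-WL or WL control groups" (Recruitment). The target is stated under Sample size: "A total of 100 adults bereaved by cancer (50 per arm) will be recruited".

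Therapy is delivered in groups. Trial design and setting says "Four groups will run online (two Non-WL and two WL", with the WL groups starting three months after the Non-WL groups. Facilitation and fidelity says "Each group will include approximately 20 to 25 participants" and gives each session two co-facilitators. Sample size says that "anticipated attrition and high demand support initial recruitment of 25 participants per group".

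Exploratory secondary analysis (between-group) defines the estimand as the between-arm difference in change from baseline over the first three months. The model is a linear mixed model (or mixed ANOVA, with ANCOVA as an option) with fixed effects for arm, time and their interaction, "and a random intercept for participants". Standardised differences with 95% confidence intervals are promised. In that sentence "group" means trial arm. The article nowhere mentions a therapy-group term, clustering or an ICC.

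Two further uses of the data matter here. Sample size says the outcomes will inform "variance estimates, and sample size planning for a future definitive RCT". Primary analysis (feasibility outcomes) summarises feasibility and acceptability with "counts, percentages, and, where appropriate, confidence intervals".

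**The concern.** During the comparison window, Non-WL participants sit in one of two rooms, with the same peers and facilitators for 12 weeks. WL participants have only an information sheet and have not yet met as a group. This is a partially nested design: outcomes may be correlated within the two treated groups and are independent in the control arm. A participant random intercept handles repeated measures on one person. It does not handle correlation between people treated together.

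The protocol itself gives reasons to expect some positive correlation. It cites peer modelling as a benefit of groups, relies on a supportive group climate for retention, and returns session feedback to facilitators to guide delivery. It also measures social disconnection as an outcome.

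Two things are at stake. One is the honesty of the reported intervals. The other is what the definitive trial inherits: if the pilot passes on only a between-person SD, planners may size the next trial as if participants were independent. Because the article spells out the random-effects structure, this is a stated choice that does not match the design, not a detail left to an analysis plan.

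**Working it through.** **Inputs from the protocol article.** 100 participants, 50 per arm; two treated groups in the window; group size m = 25 (Sample size) or 20 to 25 (Facilitation and fidelity); control arm ungrouped; participant intercept only.

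**Input assumed.** The ICC of the change score. The documents give none, so 0.01, 0.05 and 0.10 are used as a range. The SD of the change score is set to 1.

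**1. Stated sample size.** 4 groups × 25 = 100, or 50 per arm. This reproduces.

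**2. Standard error of the difference.** With two time points and complete data, the stated model amounts to a comparison of change scores.

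- As planned: √(1/50 + 1/50) = 0.200.
- With nesting in the treated arm: design effect DE = 1 + (m − 1) × ICC, and SE = √(DE/50 + 1/50).
- Ratio to the planned SE: √((DE + 1)/2).

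| ICC (assumed) | DE, m = 25 | SE | Ratio, m = 25 | Ratio, m = 20 |
|---|---|---|---|---|
| 0.01 | 1.24 | 0.212 | 1.06 | 1.05 |
| 0.05 | 2.20 | 0.253 | 1.26 | 1.21 |
| 0.10 | 3.40 | 0.297 | 1.48 | 1.40 |

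For example, at ICC 0.05 and m = 25: DE = 1 + 24 × 0.05 = 2.20; SE = √(3.20/50) = 0.253; ratio = √(3.20/2) = 1.26. For m = 20: DE = 1 + 19 × 0.05 = 1.95; ratio = √(2.95/2) = 1.21.

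**3. Coverage.** The planned comparison was simulated (40,000 runs, m = 25). The nominal 95% interval covers 94.9% at ICC 0, and 93.8% / 87.9% / 80.8% at 0.01 / 0.05 / 0.10.

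**4. Interval width at ICC 0.05.** The half-width is 1.96 × 0.200 = 0.39 SD as planned and 1.96 × 0.253 = 0.50 SD with the larger SE. If the group variance had to be estimated from the data, only 1 df lies between the two treated groups. Satterthwaite df are then about 2.1, the t quantile is 4.10, and the half-width is 4.10 × 0.253 = 1.04 SD.

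**5. Can the pilot estimate the ICC?** In the same simulation at a true ICC of 0.05, the estimate from two groups runs from about −0.04 to 0.31 (2.5th to 97.5th percentile) and is zero or negative in 49% of runs.

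**6. The SD passed on.** The expected treated-arm sample variance is 1 − ICC × (m − 1)/(2m − 1). At ICC 0.05 this is 1 − 0.05 × 24/49 = 0.9755, and the pooled SD is √((0.9755 + 1)/2) = 0.994. The SD is understated by 0.1% / 0.6% / 1.2% at ICC 0.01 / 0.05 / 0.10.

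**7. Consequence for the next trial.** As an illustration with assumed values (difference 0.5 SD, 90% power, two-sided 5%, same format, m = 25), n per arm = (1 + DE) × ((1.960 + 1.282)/0.5)². With DE = 1 this is 85. With DE = 1.24 / 2.20 / 3.40 it is 95 / 135 / 185.

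**8. Attendance.** Sessions are delivered in all four groups. For an illustrative 70% rate on n = 100, the half-width is 1.96 × √(0.7 × 0.3/100) = 9.0 points. At an assumed ICC of 0.05 for attendance it is 9.0 × √2.20 = 13.3 points.

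**The case against.** The strongest reply is that nothing decisive hangs on these intervals. The analysis is labelled exploratory and secondary, Sample size disclaims power for efficacy and promises cautious interpretation, and progression rests on feasibility and acceptability thresholds. That stands. Error rates of a 5% test or detectable differences would be the wrong yardstick, and the point is not critical. But a promise of caution does not tell a reader that a nominal 95% interval may cover 88%.

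Second, the size rests on an ICC that the documents do not give. At 0.01 the loss of coverage is negligible, and at zero the planned interval is right. Groups may also be smaller than 25 after attrition. This stands too, which is why the result is a range with both group sizes shown.

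Third, two treated groups cannot estimate the between-group variance, so the pilot could not supply that input under any model. This is correct. It argues against relying on a fitted random therapy-group effect, but not against saying that the component exists and showing what it could do.

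Fourth, the model lists its second time point as a three-month follow-up, which might be read as the assessment three months after the intervention. WL participants would then be in groups as well. The stated estimand favours the first-three-months reading. On the other reading a therapy-group component would still be absent.

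**Conclusion.** The concern holds in a limited form. In the first-three-months comparison the stated model omits the therapy-group structure of the Non-WL arm, and its intervals are too narrow for any positive ICC. The effect is trivial at an ICC of 0.01 and material from about 0.05 upwards, on the assumed range and with no loss to follow-up. Severity: should be fixed, given the exploratory status of the analysis.

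A reader might infer two stronger things that the documents do not support:

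- **That the variance estimates handed to the definitive trial are wrong.** The outcome SD is nearly right. What is missing is the between-group component. The next trial would be too small only if its planners added no design effect, and the article does not say that they will not.
- **That every feasibility interval is too narrow.** Clustering by therapy group can affect attendance and acceptability, which arise during group delivery. It does not affect WL retention or data completeness during the wait, when those participants are ungrouped. The thresholds shown in the article are stated as percentages, so wider intervals change no decision visible there; the traffic-light appendix is not shown.

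**What to change.** In Exploratory secondary analysis (between-group):

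- State that the design is partially nested: two therapy groups in the Non-WL arm, ungrouped individuals in the WL arm.
- Report Non-WL results by therapy group.
- Give each treatment effect with its 95% confidence interval over a fixed, labelled grid of assumed ICCs (0, 0.01, 0.05, 0.10), multiplying the treated-arm variance by 1 + (m − 1) × ICC with the achieved group size. Do not rely on an estimated group variance.

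In Primary analysis (feasibility outcomes), apply the same sensitivity analysis to intervals for session attendance and acceptability, and leave WL retention and data completeness during the wait as they are.

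In Sample size, state that the definitive trial's calculation must include a design effect for therapy group, with an ICC taken from outside this pilot.

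The cost is a few lines of extra analysis and wider reported intervals. Conduct and data collection do not change.

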#### Analysis population and missing data

Missing outcome data will be addressed using likelihood-based linear mixed-effects models, which use all available data and provide valid estimates under a missing-at-random (MAR) assumption [26, 55]. This approach is preferred over last-observation-carried-forward (LOCF), which relies on strong, often implausible assumptions and can bias estimates [9].

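### The exploratory treatment effect is a change-score comparison with baseline adjustment left optional, and the mixed-ANOVA option alone conflicts with the missing-data plan

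*Protocol article*

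**What the plan says.** All references are to the protocol article.

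- **Exploratory secondary analysis (between-group).** The target is stated: "The primary estimand is the difference in change between groups from baseline during the first three months". For the model, "Linear mixed-effects models (or mixed ANOVA) will be used", with group, time (baseline and three months), their interaction, and a random intercept per participant. The interaction is named as the treatment effect. Then: "Baseline scores may be included as covariates in an ANCOVA framework where appropriate". The section does not say what would make adjustment appropriate, or when a mixed ANOVA would replace the mixed model.
- **Analysis population and missing data.** Missing outcomes are to be handled by likelihood-based mixed models, "which use all available data and provide valid estimates under a missing-at-random (MAR) assumption".
- **Randomisation and allocation.** "We acknowledge how simple randomisation may result in unequal group sizes or imbalances in baseline characteristics, particularly in smaller samples". The stated response is to examine imbalances descriptively and bear them in mind when interpreting results.
- **Sample size.** "A total of 100 adults bereaved by cancer (50 per arm) will be recruited". "Although not powered for formal efficacy testing, the sample permits exploration of medium-to-large between-group differences". The outcome data are meant to inform variance estimates and the size of a definitive trial.

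**The concern.** There are two separate issues.

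**Precision and imbalance.** With two time points, the interaction is the difference between arms in mean change. A change score subtracts the whole baseline value, although only a fraction r of a baseline difference is expected to persist to month 3. It is therefore noisier than a baseline-adjusted estimate, and it over-corrects when the arms differ at baseline by chance. Simple randomisation makes such differences more likely to matter. The remedy is mentioned in the plan but left optional.

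**Missing data.** A mixed ANOVA needs both measurements from each person, so it is a completers' analysis. The missing-data section promises a method that uses everyone's available data and is valid under missing at random. The two statements cannot both govern the same analysis.

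At stake are the effect sizes, intervals and variance estimates carried into the planning of a full trial, and whether they depend on which of the permitted analyses is run.

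**Working it through.** **Inputs.** 50 per arm (Sample size). Two time points and the interaction as effect (Exploratory secondary analysis). The three-month correlation r is not given, so it is an assumption. The article's two longest-interval retest values are 0.71 over five months for self-compassion and 0.89 over six weeks for the PG-13-R. Equal variances and independent participants are assumed, which ignores any correlation within a therapy group. Outcomes are in SD units. The sample size of 100 comes with no SD, alpha, power or effect size, so there is no efficacy figure to reproduce.

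**Step 1: variance.** Per participant:
- change score: 2(1 − r)
- baseline-adjusted: 1 − r²
- ratio: (1 − r²) / [2(1 − r)] = (1 + r)/2, below 1 for every r < 1

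The 95% half-width is 1.96 × √(v × 2/50), where v is the per-participant variance.

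| r | change v | adjusted v | ratio | half-width, change → adjusted (SD) |
|---|---|---|---|---|
| 0.3 | 1.400 | 0.910 | 0.65 | 0.464 → 0.374 |
| 0.5 | 1.000 | 0.750 | 0.75 | 0.392 → 0.339 |
| 0.71 | 0.580 | 0.496 | 0.855 | 0.299 → 0.276 |
| 0.89 | 0.220 | 0.208 | 0.945 | 0.184 → 0.179 |

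In participants, the adjusted analysis of 100 matches a change-score analysis of 100/0.75 = 133 at r = 0.5, 100/0.855 = 117 at 0.71, and 100/0.945 = 106 at 0.89. A simulation of 3000 runs with 50 per arm gave ratios of 0.71, 0.76, 0.81 and 0.85 at r = 0.4, 0.5, 0.6 and 0.7, against 0.70, 0.75, 0.80 and 0.85 from the formula.

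**Step 2: chance imbalance.** If the arms differ at baseline by δ, the change-score estimate is shifted by −(1 − r)δ; adjustment removes the shift. The standard error of δ with 50 per arm is √(2/50) = 0.20 SD. At r = 0.5, an imbalance of that size moves the change-score estimate by 0.5 × 0.20 = 0.10 SD.

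**Step 3: missing month-3 data.** Simulation with r = 0.5, 50 per arm, true effect −0.50 and 300 runs. Entries are mean estimate (SD).

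| scenario | mixed ANOVA (completers) | mixed-model interaction | mixed model, common baseline mean | ANCOVA |
|---|---|---|---|---|
| nothing missing | −0.50 (0.183) | −0.50 (0.183) | −0.50 (0.164) | −0.50 (0.164) |
| about 28% missing at random chance | −0.50 (0.260) | −0.49 (0.244) | −0.49 (0.212) | −0.50 (0.212) |
| about 33% missing, depending on baseline in opposite directions by arm | −0.18 (0.248) | −0.49 (0.250) | −0.48 (0.229) | −0.48 (0.229) |

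The third row is deliberately strong. It shows the mechanism: completers differ between arms at baseline, and Step 2 applies to them. A shift of 0.32 at r = 0.5 corresponds to a completer imbalance of 0.32/0.5 = 0.64 SD. The other three methods stay close to −0.50; the Monte Carlo error is about 0.25/√300 = 0.014. With nothing missing, the first two methods coincide.

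**The case against.** The strongest reply is that this analysis is labelled exploratory, in a trial whose primary question is feasibility and which disclaims efficacy power. A lead model, an estimand and an effect index are stated, and an article may leave the covariate rule to a fuller plan. The missing-data section can also be read as settling the matter in favour of the mixed model. Much of this stands, and it limits the consequence. It does not remove the point. The article itself fixes the less precise index as the treatment effect and names an alternative that its own missing-data section rules out.

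Some stronger readings are tempting but unsupported:

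- *Baseline information is thrown away.* It is not. Baseline is the first level of time and the effect is a change from it. It is used inefficiently.
- *The whole analysis section contradicts the missing-data section.* Only the mixed-ANOVA option does. The mixed-model interaction agrees with that section, and ANCOVA stayed close to the true value under baseline-dependent dropout.
- *Mixed ANOVA would discard 30 of 100 participants.* The 70% completeness threshold is a feasibility criterion for complete outcome data, in a design that also has post-session questionnaires. It is not a month-3 loss rate. Ordinary ANCOVA also omits people without month 3, so head-count is not what separates the two. Conditioning on baseline is.
- *The model will hold baseline as both covariate and outcome.* The text speaks of an ANCOVA framework, which is a correct form. Nothing says that the two will be combined.
- *The choice will be made after seeing the data.* The article does not say when it is made. What can be said is that it gives no criterion.

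**Conclusion.** The point holds, with limited consequence. The named effect has a larger variance than a baseline-adjusted estimate at every r below 1. The reduction from adjusting is 25% at an assumed r of 0.5, and 14.5% and 5.5% at the article's retest values of 0.71 and 0.89. Those values come from retest studies, and correlations over the trial period, with an intervention in one arm, may be lower. The gain is therefore modest to material, depending on a correlation that the protocol does not give. The size rests on equal variances, complete data and independent participants.

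The mixed-ANOVA option, and only that option, is inconsistent with the missing-data section. How much bias it would cause depends on the dropout mechanism: none appeared when loss was unrelated to outcome, and it was large in the extreme scenario. Neither issue touches the primary feasibility and acceptability analysis. What is affected is the precision of the exploratory estimates used to plan the next trial, and their dependence on an unstated choice of model.

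**What to change.** 1. Delete the mixed-ANOVA alternative.
2. Replace the optional baseline clause with one prespecified model for all clinical outcomes. Preferred: a likelihood-based mixed model with baseline and month 3 as outcomes and a common baseline mean across arms (no group main effect), with the group difference at month 3 as the effect. It keeps participants who have baseline only, as the missing-data section intends.
3. If the named software (JASP) cannot fit that constraint, specify ANCOVA of month 3 on baseline, and state that it omits participants without month 3 but remains valid when dropout depends on baseline and arm.
4. State that baseline is not also entered as a covariate in a model where it is an outcome.

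The stated estimand need not change: under randomisation the baseline means are equal in expectation, so the adjusted month-3 difference and the difference in mean change target the same effect. The cost is a few sentences and a check of the software. No new data or visits are needed.

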### Participant characteristics

Demographic and bereavement-related characteristics will be summarised descriptively for the overall sample and by group using means and standard deviations for continuous variables and counts and percentages for categorical variables. These data will be used to provide context for feasibility and acceptability outcomes, including service access and potential barriers. It may also inform exploratory analyses of potential covariates or predictors of change in clinical outcomes, while emphasising that such analyses are descriptive and hypothesis-generating only [14].

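### The optional analysis of baseline severity against outcome change shows a negative association even with no treatment effect, and should be replaced by a baseline-adjusted model with a baseline-by-arm term

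*Protocol article*

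**What the plan says.** The section Exploratory secondary analysis (between-group) first sets out the treatment comparison, stating that "The primary estimand is the difference in change between groups from baseline during the first three months". It analyses this with a group-by-time model and adds an option: "Baseline scores may be included as covariates in an ANCOVA framework where appropriate".

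A separate paragraph then says that, if the sample comes close to 100, "exploratory predictor analyses may examine associations" of baseline characteristics with changes in outcome. Baseline severity is named as one of those characteristics: "associations between baseline characteristics (e.g. demographics, baseline severity) and outcome changes". The purpose is given as "This would be to inform outcome selection, covariate choice, and sample size calculations for a future trial". The limit on interpretation is "These analyses are descriptive and will not be used to draw confirmatory conclusions".

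The paragraph names the predictor and the response. It does not say that the association will be compared between arms or adjusted for baseline, and it does not mention regression to the mean.

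**The concern.** Change is the three-month score minus the baseline score, so baseline severity appears on both sides of the association. Anyone whose baseline was high partly by chance or temporary fluctuation will tend to fall back, and anyone low will tend to rise. Read literally, the planned analysis will tend to show that more severely affected participants improve more, whether or not the groups help anyone.

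The analysis has been given a job in planning the next trial, and two of its three stated uses are exposed:

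- **Outcome selection.** The size of the artefact depends on how unstable a measure is, so a less stable scale looks more predictable.
- **Sample size.** Planning needs the baseline-to-follow-up correlation and the SD. The baseline-to-change correlation is a different quantity.

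**Working it through.** **The plan's own figures.** None is given for this analysis. The only related figure is the sample size: "A total of 100 adults bereaved by cancer (50 per arm) will be recruited". It agrees with four groups of 25 (4 × 25 = 100).

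**Formula.** Let the baseline score b and follow-up score f have equal SDs (set to 1) and correlation r, with no treatment effect.

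- cov(b, f - b) = r - 1
- var(f - b) = 2(1 - r)
- corr(b, f - b) = -(1 - r)/sqrt(2(1 - r)) = -sqrt((1 - r)/2)

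**Inputs.** The article gives no three-month correlation. Its test-retest values (section Pre- and post-intervention measures) are used as stand-ins for r. The last column is the share of simulated null trials with two-sided p < 0.05 (bivariate normal scores, n = 100, 20,000 runs per value).

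| Measure | r (interval) | -sqrt((1-r)/2) | p < 0.05 |
|---|---|---|---|
| OG-SD | 0.94 (7 days) | -sqrt(0.030) = -0.17 | 41% |
| PG-13-R | 0.89 (6 weeks) | -sqrt(0.055) = -0.23 | 65% |
| PHQ-9 | 0.84 (48 hours) | -sqrt(0.080) = -0.28 | 82% |
| GAD-7 | 0.83 (1 week) | -sqrt(0.085) = -0.29 | 85% |
| PCL-5 | 0.82 (1 week) | -sqrt(0.090) = -0.30 | 87% |
| SCS | 0.71 (5 months) | -sqrt(0.145) = -0.38 | 98% |

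The quantity under the root is also the share of variance in change apparently explained: 3% to 14.5%. With no treatment effect, the measures rank in exact inverse order of stability.

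**Range for a lower three-month correlation (assumed).** Five of the six values come from intervals of six weeks or less, so r over three months is probably lower for those measures.

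- r = 0.7: -0.39
- r = 0.6: -0.45
- r = 0.5: -0.50
- r = 0.4: -0.55

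**Sensitivity to equal SDs.** If the follow-up SD is k times the baseline SD, cov(b, f - b) is proportional to kr - 1. It reaches zero only at k = 1/r, which is 1.06 for r = 0.94 and 1.41 for r = 0.71. A modest rise in spread would cancel the artefact for the most stable scale but not for the least stable.

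**Does the alternative avoid it?** Under the same null at n = 100, the baseline-by-arm interaction was significant in 4.8% to 5.3% of runs, which is the nominal level. Regression to the mean acts equally in both arms and cancels.

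**Precision of the alternative.** With 50 per arm and equal SDs, the standard error of the interaction slope is about sqrt((1 - r²)(1/50 + 1/50)) = 0.2 × sqrt(1 - r²).

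- r = 0.71: 0.2 × 0.704 = 0.141, so the 95% interval is about ±0.28
- r = 0.5: 0.2 × 0.866 = 0.173, so about ±0.34

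These are in SDs of the three-month score per SD of baseline.

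**The case against.** The strongest reply is that the text commits to little. The analysis is optional, depends on the sample size reached, and is labelled descriptive. No pooled correlation or raw change score is spelled out. The paragraph follows a group-by-time model and an ANCOVA option, so an arm-specific or baseline-adjusted form is not ruled out. This stands as a limit on how firmly the point can be put. It does not dispose of it: the article itself names baseline severity as predictor and change as response, and it states a use for the result. A cautious label also does not correct a biased estimate.

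Several stronger readings are tempting but not supported:

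- **That the artefact is strong and almost certain to appear.** The article's own reliabilities give small to moderate correlations, and at r = 0.94 fewer than half of null trials reach nominal significance. Values near -0.5 need an assumed correlation near 0.5.
- **That the next trial would restrict entry by severity.** Eligibility is not among the stated uses.
- **That covariate choice would go wrong.** Baseline score is a sound covariate and is already named for the treatment comparison. Choosing it would be right, if for a poor reason.
- **That all predictors are affected.** Demographics are not mechanically coupled to change; only variables correlated with baseline severity inherit part of the artefact. The Participant characteristics section speaks of "potential covariates or predictors of change in clinical outcomes", but its subject is demographic and bereavement characteristics, so it is not evidence of the same problem.

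On sample size, the Sample size section separately lists variance estimates among the pilot's aims, and the planned mixed model can supply them. With equal SDs, r can also be recovered as 1 - 2c², where c is the baseline-to-change correlation. The needed figures are therefore obtainable. The flaw is that the predictor analysis is offered as a source for them.

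**Conclusion.** The point holds, with limits. An association between baseline severity and change from that baseline is negative with no treatment effect: about -0.17 to -0.38 with the article's test-retest values as the baseline-to-follow-up correlation, and larger if the three-month correlation is lower. This rests on equal SDs at the two times and on short-interval reliabilities standing in for a three-month correlation that the article does not give.

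The result could misinform outcome selection and is the wrong input for sample size. To say that it would misinform the next trial goes too far, because the analysis may not be run and is not meant to support confirmatory conclusions. The primary feasibility and acceptability outcomes and the between-group comparison are not touched.

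**What to change.** Revise the predictor paragraph in Exploratory secondary analysis (between-group) to say:

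1. For baseline severity, regress the three-month score on baseline score, arm and baseline-by-arm interaction. Read any differential benefit from the interaction and its confidence interval. The slope in the waitlist arm shows the regression to the mean expected without the intervention.
2. For other baseline characteristics, use the three-month score adjusted for baseline score and arm, in place of raw change.
3. For planning, report the baseline-to-three-month correlation and the residual SD for each outcome.

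The cost is a few sentences, with the same data and software. The drawback is that the interaction will be imprecise at n = 100, so it should be reported as an estimate with its interval.
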